**São Paulo, SP**

**2023**

**ABSTRACT**

Among the various complications of the postoperative evolution of fractures of the proximal humerus (FUP) are pain and joint stiffness, generating significant functional limitation in the affected limb. Physical therapy is the standard treatment for both surgical and non-surgical cases. Studies have shown positive effects of photobiomodulation (PBM) on repair and regeneration of fractures, as well as on analgesia and functional improvement. However, they suggest standardization and additional evidence. This randomized controlled double-blind clinical study will aim to evaluate the effects of PBM on the functional recovery of participants with FUP surgically treated with special locking plates. The 42 participants will be randomized (1:1) into 2 groups, the Control group (standardized physiotherapy treatment associated with simulated PBM) and the PBM group (standardized physiotherapy treatment associated with active PBM). The PBM will be applied by the participant at home every day, for 10 minutes, using a device containing 318 LEDs light emitting diodes, 159 LEDs of 660 nm (28.5 mW; 12 J/cm2; 17 J per LED) and 159 850 nm LEDs (23 mW; 10 J/cm2; 14 J per LED). The PBM and physiotherapy sessions (30 minutes, 2 times a week) will be held for 12 weeks. Participants will not be aware of their allocation and will be assessed at 24h, 1, 2, 4, 8 and 12 weeks after the surgical procedure by 4 examiners who are also blinded to each participant's allocation. The main outcome, evaluated in all experimental periods, will be the recovery of shoulder function using the Quick-DASH functional scale. Secondary outcomes will be assessments of range of motion of the shoulder using a digital goniometer, quality of life using the SF-6 questionnaire and the occurrence of adverse effects in all experimental periods. Spontaneous pain, pressure pain (dolorimeter), nocturnal pain and the use of analgesics will be evaluated at 1, 2, 4, 8 and 12 weeks; consolidation of fractures at 4, 8 and 12 weeks through radiographic examinations; and muscle strength by progressive weight bearing at 8 and 12 weeks. In addition to punctual evaluations, each participant will be monitored daily through telephone contact. The collected data will be stored, organized in a repository and the appropriate statistical tests will be applied for each specific analysis. In all tests, a significance level of 5% will be adopted.

Keywords: Photobiomodulation, Humeral Fracture, Quick-DASH, Quality of life, Phototherapy

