**Evaluation of Therapeutic Success in PHF Treatment**

Even after surgical or conservative treatment, PHF can still cause pain, limitations in daily activities, limb disability, and reduced quality of life. Clinical trials on PHF often report diverse outcomes, complicating treatment comparisons and consensus development (Nowak et al., 2019; Richard et al., 2020).

It has been suggested that the evaluation of therapeutic success in PHF treatment should primarily reflect the restoration of patients' daily activities, using tools known as Patient Reported Outcomes (PRO). For PHF follow-up, it is recommended to include at least one functional score (e.g., DASH - Disabilities of the Arm, Shoulder, and Hand; ASES - American Shoulder and Elbow Surgeon’s Score; or Oxford Shoulder Score) and PROs reflecting health status and quality of life, such as the EQ-5D - EuroQol-5 Dimension and the SF-6D - Short Form-6 Dimension (Nowak et al., 2019; Richard et al., 2020).

The DASH functional disability index, developed in 1996, is a self-administered instrument for measuring symptoms and physical function of the upper limbs. It can be used for clinical and research purposes. The DASH consists of questions related to daily activities, symptoms, and social/role functions over the past week. The 30 questions are scored on a scale of 1 to 5 points, with a total score ranging from 0 (no difficulty) to 100 (significant difficulties/disabilities) (Hudak et al., 1996). This tool has been adapted into over 50 languages and extensively validated in numerous scientific articles (Kennedy & Beaton, 2017; Richard et al., 2020). DASH has demonstrated strong reliability, moderately strong validity, and high psychometric properties in evaluating PHF patients (Slobogean et al., 2010; van de Water et al., 2014).

A shorter version, Quick DASH, was released in 2005, containing 11 items (Beaton et al., 2005). Like the original version, Quick DASH offers five response options and a total score of 100 points. Both questionnaires have optional modules, scored separately, designed for athletes/performers and work-related assessments (Kennedy & Beaton, 2017). Quick DASH can replace DASH for evaluating upper extremity disorders with similar accuracy, offering easier and faster administration (Beaton et al., 2005; Gummesson et al., 2006).

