**3.1. Primary Objective**

The primary outcome of the study is to assess the functional recovery following proximal humeral fractures treated with ORIF, stabilized with fixed-angle plates, and managed with physiotherapy and photobiomodulation. This will be evaluated using the Brazilian version of the Quick DASH (Disabilities of the Arm, Shoulder, and Hand) questionnaire.

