**QuickDASH Score Calculation**:

QuickDASH Score=[(Sum of responsesn)−1]×25\text{QuickDASH Score} = \left[\left(\frac{\text{Sum of responses}}{n}\right) - 1\right] \times 25QuickDASH Score=[(nSum of responses​)−1]×25

Where nnn is the number of answered questions.

The QuickDASH will be administered at 1, 2, 4, 8, and 12 weeks post-surgery.

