**2. Data Analysis**

Initial descriptive analyses will be performed considering all variables measured in the study, both quantitative (mean and standard deviation) and qualitative (frequencies and percentages). Subsequently, normality tests will be conducted to determine the appropriate statistical tests for each data set. Appropriate statistical tests will then be applied for each specific analysis.

Subgroup analyses will also be performed, considering variables such as the presence of osteoporosis, osteopenia, high- and low-intensity traumas, smoking, and other comorbidities.

A significance level of 5% probability or the corresponding p-value will be adopted for all tests. All analyses will be conducted using the **SAS for Windows** statistical software, version 9.1.

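### No primary time point or single contrast is fixed for QuickDASH while every test gets 5%, and the protocol's QuickDASH schedules disagree about 24 h

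*Protocol*

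**What the plan says.** On the main outcome, the Abstract says: "The main outcome, evaluated in all experimental periods, will be the recovery of shoulder function using the Quick-DASH functional scale". Its list of periods is that participants "will be assessed at 24h, 1, 2, 4, 8 and 12 weeks after the surgical procedure", which makes six.

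Section 3.1 (Primary Objective) reads: "The primary outcome of the study is to assess the functional recovery following proximal humeral fractures treated with ORIF". It names QuickDASH as the instrument but gives no visit and no summary over visits. The hypotheses in section 2 (Justification) say only that PBM is, or is not, effective after surgery.

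Section 4.15.1, under the score calculation, says: "The QuickDASH will be administered at 1, 2, 4, 8, and 12 weeks post-surgery". That is five visits, without 24 h. The opening of the same section places the questionnaire in Appendices 3 to 8, among others.

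On the error rate, the Abstract says: "In all tests, a significance level of 5% will be adopted". The Data Analysis section says: "A significance level of 5% probability or the corresponding p-value will be adopted for all tests". That section leaves the choice of test until normality has been checked. A mixed-effects regression model appears only in section 4.14, for participants who stop treatment or miss contacts.

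**The concern.** Three statements combine badly. All periods have equal standing as the main outcome, the hypothesis is met by any evidence of efficacy, and each test may use the full 5%. Nothing in the text prevents the trial from being declared positive on the one visit that reached p < 0.05, whichever visit that was. A reader could not then tell a confirmed effect from the best of five or six looks at the same question.

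Separately, the sections do not agree on when the main outcome is collected. The disputed visit is the one that falls at the start of treatment. If it counted as an outcome visit, it would add a comparison that can only be positive by chance or through baseline imbalance.

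**Working it through.** **Step 1: what is fixed.** The significance level is 5% for all tests (Abstract; Data Analysis). Sidedness is not stated; I assume two-sided. The sample size is 21 per group with 15% loss (section 4.5), so 42 × 0.85 / 2 = 17.85, or about 18 evaluable per arm. No between-visit correlation is given; I assume 0.3 to 0.9.

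**Step 2: one comparison.** A single prespecified test at 5% has a 5% false-positive rate. This is the plan's own figure.

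**Step 3: one test per visit, upper bound.** If visits were independent, the chance of at least one false positive is 1 − (1 − 0.05)^k.
- k = 5: 1 − 0.95^5 = 22.6%
- k = 6: 1 − 0.95^6 = 26.5%

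**Step 4: one test per visit, correlated scores.** I simulated trials with no treatment effect, 18 per arm, and a two-sided t-test at 5% at each visit (40,000 trials per row). I used either equal correlation between all visits or correlation that decays with visit distance (AR(1), where the value shown is for adjacent visits).

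| Assumed correlation | Five visits, equal | Five visits, AR(1) | Six visits, equal | Six visits, AR(1) |
|---|---|---|---|---|
| 0.3 | 21.0% | 21.8% | 24.3% | 25.0% |
| 0.5 | 18.6% | 20.2% | 21.0% | 23.6% |
| 0.7 | 15.0% | 17.3% | 17.0% | 20.4% |
| 0.8 | 12.9% | 15.0% | 13.9% | 17.3% |
| 0.9 | 10.3% | 12.2% | 10.9% | 13.5% |

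For the five visits after treatment starts, the range is about 10–22%. A normal-theory simulation with 1,000,000 draws agrees (equal correlation, five visits: 18.2% at 0.5, 12.8% at 0.8, 10.2% at 0.9).

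**Step 5: the schedules side by side.**
- Abstract: 24 h and weeks 1, 2, 4, 8, 12 (six visits).
- Section 4.15.1, score calculation: weeks 1, 2, 4, 8, 12 (five visits).
- Section 4.15.1, opening: recorded in Appendices 3 to 8, among others. Section 4.15.2 uses those forms for day 1 and the five later visits, and section 4.15.3 ties Appendices 7 and 8 to weeks 8 and 12. So these are six visit forms, the first for day 1.

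The form reference supports the Abstract but does not settle the matter. Section 4.15.6 cites the same six forms for quality of life while listing only five visits, and the appendices are not available here.

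**Step 6: what a 24 h score can be.** Section 4.7 opens the envelope 24 h after surgery, when the device is delivered. Section 4.12 starts PBM at 24 h. A score at that point precedes, or at best coincides with, the first application. It can serve as a baseline but not as an outcome.

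**The case against.** The strongest reply is that evaluating an outcome at every period means measuring it there, not testing it there. No section prescribes a group comparison at each visit. A single group effect or group-by-time test in a longitudinal model would keep 5%, and section 4.14 shows that the authors have such a model in mind. An analysis plan may also exist that settles this. Part of that stands: a reader might infer that the trial's false-positive rate is already 13–26%, but the documents do not support so firm a statement. The inflation is a risk that the text leaves open. The 26% end needs six nearly independent visits, including 24 h, which is implausible for one questionnaire repeated in the same patients.

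Other tempting extensions also fail:
- The schedule conflict does not cause the inflation; it only changes the count from five to six.
- A figure for lost power would have to be built on an effect size that section 4.5 does not give and on a correction that nobody proposes.
- A claim that averaging over six visits would dilute the effect presupposes an analysis that the protocol does not describe.
- A recall-period argument against the 24 h score would rest on "The DASH consists of questions related to daily activities, symptoms, and social/role functions over the past week", which describes the full DASH; no recall period is given for QuickDASH.
- The absence of a bone-density test from the admission work-up in section 4.8 does not rule out osteoporosis subgroups, since medical history could define them.
- Error control for secondary outcomes and subgroups may properly be left to an analysis plan.

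What the reply does not remove is that the protocol gives every period main-outcome status, fixes 5% for all tests, and mentions the mixed model only for incomplete participants, without naming a contrast.

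**Conclusion.** The point holds in this form: the protocol does not fix which QuickDASH comparison decides the trial, and its blanket 5% rule would let efficacy be claimed from any visit. If the five visits from week 1 to week 12 were each tested at 5%, the overall false-positive rate would be about 10–22%, two to four times the stated level. This is conditional on visit-by-visit testing, two-sided tests, about 18 evaluable per arm and an assumed correlation of 0.9 to 0.3. The 22.6% bound for independent visits is the ceiling for five visits under these correlation patterns.

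The disagreement between the Abstract and section 4.15.1 over a 24 h QuickDASH is a separate contradiction and needs no assumption. Both should be corrected, because the primary comparison is what the trial's conclusion rests on.

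**What to change.** Before unblinded data are seen:

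1. Name one primary comparison in the Abstract, section 3.1 and the Data Analysis section, at two-sided 5%. Two suitable choices are the between-group QuickDASH difference at week 12, when PBM and physiotherapy end, or one prespecified contrast from a mixed-effects model fitted to all participants. Either restores 5% for the main question.
2. Make the remaining QuickDASH visits secondary.
3. Reconcile the Abstract, both parts of section 4.15.1 and the visit forms on the 24 h QuickDASH. If it is kept, collect it before the envelope is opened and use it only as a baseline covariate. If it is not kept, remove it from the Abstract and from the day-1 form.

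The cost is wording in the protocol and the matching registration entry; no extra participants are needed. The downside is small: an early effect that fades before the primary time point would be reported as a secondary result.

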**LIST OF TABLES**

Table 1. Randomized Controlled Clinical Trials on PBM in Bone Fractures................... 32
Table 2. Dosimetric Parameters of the PBM Device...................................................... 32
Table 3. Treatment Costs.............................................................................................. 38

LIST OF ABBREVIATIONS AND ACRONYMS

ADM ....... Range of Motion

AMP ....... Adenosine Monophosphate

AO ....... Arbeitsgemeinschaft fur Osteosynthesefragen (German for the Association for the Study of Internal Fixation)

ASES ....... American Shoulder and Elbow Surgeon’s Score

ATP ....... Adenosine Triphosphate

CEP ....... Research Ethics Committee

CONSORT ....... Consolidated Standards of Reporting Trials

DASH ....... Disabilities of the Arm, Shoulder and Hand

ECR ....... Randomized Clinical Trial

EQ-5D ....... Euroqol-5Dimension

EROS ....... Reactive Oxygen Species

EVA ....... Visual Analog Scale

PBM ....... Photobiomodulation

FUP ....... Proximal Humerus Fractures

HMACN ....... Municipal Hospital Alípio Correa Netto

ICC ....... Intraclass Correlation Coefficient

LEDs ....... Light Emitting Diodes

OTA ....... Orthopaedic Trauma Association

PRO ....... Patient Reported Outcomes

ProFHER ....... Proximal Fracture of Humerus: Evaluation by Randomisation

RAFI ....... Open Reduction and Internal Fixation

SF36 ....... 36-Item Short-Form Health Survey

SF6D ....... Short-Form 6 dimension

SPIRIT ....... Standard Protocol Items: Recommendations for Interventional Trials

TCLE ....... Free and Informed Consent Form

TRP ....... Transient Receptor Potential

**1. CONTEXTUALIZATION**

Fractures of the proximal humerus (FUP) are those that occur in the surgical neck (the narrowing just below the greater and lesser tuberosities of the humerus) or in regions proximal to it. Their incidence varies depending on the geographic region and the date of data collection, but in general, they represent about 5 to 10% of all bone fractures in the body (Court-Brown & Cesar 2006, Relvas Silva et al 2021, Iglesias-Rodríguez et al 2021). The incidence of FUP tends to increase with age and is identified as the third most frequent fracture in the population over 65 years of age, depending on the state of health, level of activity, and care received (Roux et al 2012, Relvas Silva et al 2021, Iglesias-Rodríguez et al 2021).

In older adults, most FUP cases are related to low-energy traumas, primarily due to falls from their own height or direct trauma to the lateral aspect of the shoulder. In these cases, women are more affected due to longer life expectancy and osteoporosis (Barbosa et al 2008, Iglesias-Rodríguez et al 2021). In individuals under 55 years, traumas leading to FUP tend to be of higher energy, and their distribution is not as affected by gender (Iglesias-Rodríguez et al 2021).

**Classification**

The primary classifications used for proximal humeral fractures are Neer and AO/OTA. Neer's classification (1970) defined the four fracture fragments: head, greater and lesser tuberosities, and diaphysis. Fractures are considered displaced when the fragments are displaced at least 1 cm or angulated at a minimum of 45°. Thus, fractures can be classified as non-displaced and displaced/dislocated in 2, 3, or 4 parts, as follows (Carrerra et al 2012, Petros et al 2019):

Group I: Minimally displaced fracture (displacement less than 1 cm or angulation less than 45°).

Group II: Displaced fracture (more than 1 cm of displacement or more than 45° of angulation). Fragment = anatomical neck of the proximal humerus.

Group III: Displaced fracture (more than 1 cm of displacement or more than 45° of angulation). Fragment = surgical neck of the proximal humerus.

Group IV: Fracture with displacement of the greater tuberosity of the humerus (more than 1 cm of displacement or more than 45° of angulation).

2 parts: (no displacement of the surgical neck);

3 parts: (displacement of the surgical neck);

4 parts: (displacement of the surgical neck and lesser tuberosity).

Group V: Fracture with a displacement of the lesser tuberosity (more than 1 cm of displacement or more than 45° of angulation).

2 parts: (no displacement of the surgical neck);

3 parts: (displacement of the surgical neck);

4 parts: (displacement of the surgical neck and lesser tuberosity).

Group VI: Fracture associated with glenohumeral dislocation and can also be subdivided into two, three, or four parts.

The AO/OTA classification is an alphanumeric structure based on imaging exams (X-rays, tomography, and, if necessary, magnetic resonance imaging). Each bone is defined by a number, and for the humerus, it is number 1. The location of the fracture within the bone is also defined by numbers: proximal segment (1), diaphysis (2), and distal segment (3), following Heim's square system. Regarding the type of fracture, it is classified as extra-articular unifocal or two parts (A), extra-articular bifocal or three parts (B), and articular or four parts (C) as follows (Carrera et al 2012):

**11 - Proximal humerus region**

A - Extra-articular unifocal

A1: Tuberosities

A1.1 - Greater tuberosity

A1.2 - Lesser tuberosity

A2: Surgical neck

A2.1 - Simple

A2.2 - Wedge

A2.3 - Multifragmented

A3 - Vertical

**11B - Extra-articular, bifocal**

B1: Surgical neck

B1.1 - With greater tuberosity

B1.2 - With lesser tuberosity

**11C - Articular or four parts**

C1: Anatomic neck

C1.1 - Impacted in valgus

n - Greater tuberosity

o - Lesser tuberosity

p - Both

C1.2 - Isolated neck

**Treatment**

The treatment of proximal humeral fractures (PHF) remains controversial and can be technically challenging, often requiring significant resources and care depending on factors such as fracture complexity, bone quality, functional demands, patient age, and comorbidities (Ziegler et al., 2020; Iglesias-Rodríguez et al., 2021; Relvas Silva et al., 2021; Handoll et al., 2022).

A recent systematic review evaluated the best methods to restore shoulder function and avoid adverse treatment outcomes. The review included 47 studies (3,179 participants with shoulder fractures, most of whom were women aged 60 years or older) conducted across 21 countries, with most studies following participants for at least one year. The authors concluded that there is still insufficient scientific evidence from randomized controlled trials to support definitive choices between conservative treatment and various surgical modalities for these fractures. Furthermore, even regarding conservative treatment, there was no conclusive evidence that one week of immobilization is better or worse than three or more weeks (Handoll et al., 2022).

In clinical practice, non-displaced or minimally displaced and stable fractures are typically eligible for conservative treatment, involving sling use for one or more weeks followed by rehabilitation. Conversely, displaced, unstable, open fractures or those associated with vascular injuries are generally treated surgically (Ratajczack et al., 2019; Petros et al., 2019; George et al., 2021; Handoll et al., 2022).

Surgical treatment involves various stabilization techniques, including pin fixation, rods, plates, or arthroplasty. A recent systematic review comparing outcomes of these techniques for displaced PHF found no significant differences among them or between them and conservative treatment. However, some trends emerged: Hemiarthroplasty showed better results in quality of life. Reverse arthroplasty demonstrated superior outcomes in abduction, flexion, Constant score, and lower rates of malunion, osteonecrosis, and the need for surgical reintervention. Open reduction and internal fixation (ORIF) yielded better results in the Quick-DASH disability score and the visual analog scale for pain (Davey et al., 2022).

ORIF with locking plates aims to preserve vascularization and stabilize fracture fragments sufficiently to allow early mobilization, resulting in a lower rate of reduction loss (Oldrini et al., 2022; Petros et al., 2019). In a series of 33 patients treated with angular stability locking plates for PHF, Monteiro et al. (2011) reported 91.2% excellent and good results using the UCLA (University of California at Los Angeles) functional score, deeming the method effective for stabilizing PHF without additional complications.

Ockert et al. (2014) described outcomes in 43 cases of displaced and unstable PHF classified according to Neer and AO/OTA criteria, treated with locking plates. After ten years of surgical treatment, most patients exhibited excellent or good results, with poor long-term outcomes occurring mainly in elderly female patients.

In a series of 35 cases treated with fixed-angle locking plates, George PK et al. (2021) concluded that effective stability achieved during surgery, maintained throughout follow-up, allowed early mobilization. This resulted in better range of motion (ROM) and quicker return to activities, with minimal reduction loss compared to other implants.

Another systematic review in the same year analyzed the best approaches to restore shoulder function and prevent adverse treatment outcomes, also evaluating 47 studies (3,179 participants, mostly older women) across 21 countries. Similar to earlier findings, the review concluded that there remains insufficient evidence from randomized controlled trials to guide decisions between conservative and surgical treatment modalities for PHF. Additionally, no definitive evidence was found to support the superiority of one or three weeks of immobilization during conservative treatment (Handoll et al., 2022).

